# Culturally specific versus standard group cognitive behavioral therapy for smoking cessation among African Americans: an RCT protocol

**DOI:** 10.1186/2050-7283-1-15

**Published:** 2013-08-21

**Keywords:** Smoking cessation, African Americans, Culturally specific, Cognitive behavioral therapy

## Abstract

**Background:**

African American smokers experience disproportionately higher rates of tobacco-related illnesses compared to Caucasians. It has been suggested that interventions targeted to specific racial/ethnic groups (i.e., culturally specific) are needed; however, the literature examining the efficacy of culturally specific interventions is equivocal. Moreover, there are few descriptions of methods used to create these interventions. The main aim of this study is to test the efficacy of a culturally specific smoking cessation intervention among African Americans.

**Methods/Design:**

A 2-arm randomized controlled trial (RCT) will be conducted to assess the efficacy of a culturally specific group cognitive behavioral therapy (CBT), compared to standard group CBT among treatment-seeking smokers from the community. Participants in both conditions receive the transdermal nicotine patch (TNP) for 8-weeks. We intend to randomize at least 247 adult smokers who self-identify as African American into the trial. Enrolled participants are block randomized into one of two groups: Standard group CBT (control) or a culturally specific group CBT (CS-CBT). Groups are matched for time and attention, and consist of eight sessions. The primary outcome variable is 7-day point prevalence abstinence (7-day ppa). Smoking status is assessed at the end-of-counseling (EOC), and 3, 6, and 12-month follow-ups, with self-reported abstinence verified by saliva cotinine. We hypothesize that the CS-CBT condition will produce significantly greater smoking cessation rates compared to the control condition. We also expect that this effect will be moderated by acculturation and ethnic identity, such that the CS-CBT will show the greatest effect on cessation among participants who are less acculturated and have greater ethnic identity.

**Discussion:**

Answering the fundamental question of whether culturally specific interventions lead to incremental efficacy over established, evidence-based approaches is of utmost importance. This study will have implications for the development and implementation of smoking cessation interventions among African Americans and other racial/ethnic minority groups.

**Trial registration:**

NCT01811758

## Background

### Significance

In 2011, 19.4% of African American adults were current smokers (CDC 2012). Although comparable to the overall population, the prevalence among low-income African Americans is notably higher (40%-60%) (Delva et al. 2005). In addition, African American smokers experience disproportionate rates of smoking-related disease and death compared to other racial-ethnic groups (Park et al. 2011;American Cancer Society 2007). Smoking characteristics differ between African Americans and Caucasians, some of which may help explain these disparities in health. It is known that compared to Caucasian smokers, African Americans are more likely to smoke mentholated brands, have higher serum cotinine concentrations per cigarette smoked (Caraballo et al. 2011), are less likely to use evidence-based cessation treatments and are less likely to achieve cessation (Fu et al. 2008;Trinidad et al. 2011). The latter points may in part be attributable to the lower likelihood of receiving appropriate smoking cessation advice from providers (Lopez-Quintero et al. 2006) and the failure of prior interventions to address ethno-cultural factors that may limit their effectiveness. Needed are evidence-based interventions that specifically target African American smokers. The purpose of this study is to evaluate the incremental efficacy of addressing unique ethno-cultural factors within the context of an established cognitive behavioral therapy for smoking cessation in a sample of African Americans.

### Cognitive behavioral therapy for smoking cessation

Cognitive behavioral therapy (CBT) for smoking cessation and relapse prevention have established efficacy (Fiore et al. 2008;Song et al. 2010). CBT for smokers includes a focus on coping skills training, and has efficacy at least comparable to pharmacotherapy (Fiore et al. 2008), with greater cost-effectiveness (Cromwell et al. 1997). Group-based CBT is particularly efficacious, and provides social support, positive reinforcement, psychoeducation, and cognitive behavioral strategies for coping and stress management (Stead & Lancaster 2005). Little previous research has examined group smoking interventions with CBT components among African American. Two studies found evidence for efficacy when compared to assessment only and minimal self-help (Murray et al. 2001;Knight 2004). Only one trial compared CBT to a time-and-attention matched control condition (Webb et al. 2010), which was the first study to demonstrate that CBT was causally related to smoking cessation among African Americans. However, because the intervention was delivered using a standard (i.e., non-culturally specific) format, it did not address the unique ethno-cultural characteristics of African American smokers. Indeed, this standard intervention had lower efficacy among the subgroup of smokers with traditional African American values and cultural practices (Webb Hooper et al. 2012).

### Culturally specific smoking cessation interventions

Culturally specific approaches to behavior change integrate race, ethnicity, social factors, culturally traditional norms and values, and behavior patterns into the core of interventions. Such interventions have been referred to using various terms, including culturally sensitive, targeted, tailored, and competent. This study uses the term culturally specific to convey that the intervention is designed for a specific ethno-cultural group (i.e., African American smokers), yet may not apply equally to all members. Models of culturally specific interventions targeting African Americans emphasize the significance of framing the content and presentation within a context that is appropriate for the group (Kreuter et al. 2002;Resnicow et al. 1999). Resnicow and colleagues (1999) described two components of culturally sensitive interventions, surface and deep structure. The goal of surface structure is to adapt the presentation of interventions to facilitate acceptability, receptivity, and capture attention (e.g., race-matched images). In contrast, deep structure adapts the intervention content by addressing meaningful historical, socio-cultural, environmental, and psychological factors (e.g., collectivism, religion, and racism). The intervention in the current study includes both surface and deep structure elements.

More research is needed to test culturally specific interventions for African American smokers. A few studies have compared culturally specific self-help materials to standard control groups, and found a preference for the culturally specific booklets (Webb 2009;Orleans et al. 1998) and greater quit attempts among participants in the culturally specific condition (Orleans et al. 1998;Nollen et al. 2007). These studies did not find smoking cessation differences between conditions, which is the primary goal of most interventions. It is possible that adapting existing interventions with demonstrated efficacy among African American smokers will add incremental efficacy to outcomes. This assertion is supported by previous research in the psychotherapy literature indicating that culturally specific interventions are more effective than traditional interventions, and that this effect is positively associated with the extent of specificity (Smith et al. 2011).

### Consideration of ethno-cultural individual differences

Because race is not equivalent to a monolithic culture, culturally specific smoking cessation interventions may benefit some smokers, but not others (Webb 2008). It is important to consider individual differences in acculturation (i.e., the extent of engagement in one’s traditional cultural beliefs, values, and practices versus adoption of the dominant culture) and ethnic identity (i.e., identification and affiliation with one’s ethnic group), as these factors may affect outcomes. African American smokers are likely to be less acculturated compared to African American non-smokers (Klonoff & Landrine 1999;Landrine & Klonoff 1994). Acculturation is also predictive of culturally specific intervention receptivity. Webb (2008) found that less acculturated African American smokers preferred culturally specific written materials, while those higher on acculturation preferred standard materials. Ethnic identity also has the potential to influence outcomes following culturally specific interventions. Resnicow et al. (2009) found that tailoring a self-help nutrition newsletter on ethnic identity resulted in improved fruit and vegetable intake among Afrocentric African Americans. No previous research has examined the role of ethnic identity in culturally specific interventions among smokers. This study, however, will explore the possibility that culturally specific CBT will be more efficacious among smokers with greater ethnic identity.

### The present study

This study will address an important gap in the literature by answering a fundamental question regarding the use of culturally specific interventions among African American smokers in a randomized controlled trial. Previous research suggests a positive role of cultural specificity for process outcomes in self-help trials, but no studies have demonstrated a significant effect on smoking cessation within more potent interventions (e.g., group CBT). We hypothesize a main effect of cultural specificity, such that CS-CBT will result in greater smoking cessation rates compared to standard CBT. We also expect to find a main effect of time, such that the CS-CBT condition will result in greater cessation rates through 12-months. We do not anticipate an intervention × time interaction. Our exploratory analyses will consider the moderating roles of acculturation and ethnic identity on smoking cessation outcomes. Specifically, we expect that less acculturated participants (i.e., highly engaged in traditional African American culture) and those with greater ethnic identity will show the greatest cessation rates if they are in the CS-CBT condition.

## Design and method

This phase 1 efficacy study is a 2 (intervention) × 4 (time) mixed factorial design with cotinine-confirmed cessation as the primary outcome. Factor 1 is the type of intervention: culturally specific CBT (CS-CBT) versus standard CBT (control), both supplemented by 8-weeks of transdermal nicotine patch (TNP) therapy. CBT in both conditions consists of cognitive and behavioral strategies guided by evidence-based smoking cessation and relapse prevention models (Marlatt & Gordon 1985). The key difference between conditions is whether the intervention is culturally specific. The culturally specific components (e.g., discussion of race and smoking, race-matched clinicians, and an emphasis on religion/spirituality) are those described in the literature and our prior research. Factor 2 is time: End-of-counseling (EOC), and 3, 6, and 12-month post counseling assessments. This study includes a controlled, internally valid, experimental test of the efficacy of CS-CBT among African American smokers. Figure 1 illustrates the flow of participants through the trial.

**Figure 1 Fig1:**
[figure not shown]
**RCT flowchart.** Illustration of study design and participant flow.

### Participants and recruitment

Participants will be 247 African American tobacco smokers recruited from the community. We developed a comprehensive recruitment plan, consisting of advertisements on public transportation, partnering with healthcare organizations with large racial minority clientele, and street outreach (directly talking with people in predominantly Black neighborhoods and visiting local businesses). Participants are considered eligible if they: (1) self-identify as African American; (2) currently smoke ≥ 5 cigarettes/day or have an expired CO level of ≥ 8 ppm; (3) are ages 18–65; (4) are able to read 5^th^-6^th^ grade English; (5) have permanent contact information; (6) are able to attend clinic sessions (transportation costs are reimbursed); and (7) are motivated to quit smoking (rated as a 6 on a 1–10 scale). We exclude those who are currently receiving any type of cessation, alcohol or illicit drug treatment, pregnant/breastfeeding, or diagnosed with an acute cardiac or respiratory condition. Ineligible participants are referred to the Florida QuitLine.

### Randomization

Eligible participants are randomly allocated using a 1:1 ratio in blocks of 50 to one of the two conditions, CS-CBT or control. The unit of randomization is the individual. Eligible participants receive a tentative random assignment and are scheduled for an orientation session, with only those who attend and provide written informed consent enrolled in the study. We schedule up to 25 participants per group to ensure 8–12 tentatively assigned participants are enrolled/consented into the study.

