### Interventions

#### Orientation and intervention sessions

Participants attend a 60-minute orientation before the start of the clinic sessions. They learn the background, purpose, format, and procedures of the study; provide informed consent; complete baseline measures; learn about TNP therapy and receive their first patch (the remainder of the patches are provided throughout active treatment); and provide breath carbon monoxide (CO) and saliva samples for cotinine analysis. We also cover smoking and health, self-motivation, and goal setting. In the CS-CBT condition, we explain that the group is framed within a cultural context, designed to emphasize African American race/ethnicity and cultural issues.

In accordance with previous research (Webb et al. 2010;Brandon et al. 1995) participants in both conditions are asked to reduce their smoking by one-half on the day before the first clinic session and to abstain completely from smoking on the first day of actual group treatment (session 1). They are also instructed to begin patch use on the morning of the first day of treatment (session 1; the target quit day) with the patch provided at orientation. This aspect of the protocol is unique from other cessation approaches that set the quit day several weeks post beginning the intervention. However, this evidence-based protocol has been successful in previous studies [e.g., Webb et al. 2010; Brandon et al. 1995 and is also the format we use in our ongoing cessation clinic. Participants who do not quit on the target day are encouraged to make a quit attempt by the third treatment session.

Participants in both conditions meet eight times over four consecutive weeks. Four sessions occur during week 1, two during week 2, and one weekly booster session during weeks 3 and 4. Depending on group size, the duration of sessions is 90–120 minutes in both conditions. We anticipate 8–16 participants per group. Co-therapy pairs of masters or bachelor’s level interventionists are trained to conduct sessions for one condition (CS-CBT or control) and supervised by the principal investigator (PI). Groups are held in a laboratory-based clinic. Incentives include $40 at session 1, $20 at session 5, $50 at session 8, $50 at the 3-month assessment, $70 at the 6-month assessment, and $70 at the 12-month assessment. Participants also receive $5 per session for transportation/parking and light refreshments at each session.

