**Table 1 Tab1:** **Overview of the interventions**

	CBT	CS-CBT
**Orientation**	Study explanation, structure of sessions and TNP, informed consent, health and smoking, research participation, goal setting, baseline assessment, breath carbon monoxide (CO) and saliva samples.	Same as in the CBT condition. Race and smoking, views on research participation, distrust for biomedical research, concerns about nicotine replacement, goal setting, baseline assessment, breath CO and saliva samples, race-matched clinicians (RMC).
**Session 1**	Review quit plan, positive reinforcement (PR), reasons for quitting, nicotine addiction, introduction to coping response training model, smoking and motivation, TNP use, plan for next 24 hours, behavioral contracting (BC), CO.	Standard CBT. Meaning of being African American, tobacco and African Americans, menthol, RMC.
**Session 2**	Review quit plan progress, PR, benefits of quitting, coping skills, plan for next 24 hours, BC, CO.	Standard CBT. Spirituality and religion in the African American community, RMC.
**Session 3**	Review quit plan progress, PR, stress management, alcohol and smoking, high cost of smoking, plan for next 48 hours, perceived benefits of quitting, BC, CO.	Standard CBT. Stressors unique to African Americans, discrimination and racism, deep breathing exercises, co-morbid addiction, little cigars and blunt use, RMC.
**Session 4**	Review quit plan progress, PR, negative affect and smoking, cognitive restructuring, decision making, plan for next 72 hours, BC, CO.	Standard CBT. Traditional African American values, buddy system, deep breathing exercise, RMC.
**Session 5**	Review quit plan progress, PR, review personal high-risk situations, relapse prevention, responding to lapses, plan for next 72 hours, BC, CO.	Standard CBT. Mood and depression among African Americans, deep breathing exercise, RMC.
**Session 6**	Review quit plan progress, PR, individual high-risk situations, noted benefits of quitting, weight and smoking cessation, minimizing weight gain, relapse prevention, plan for next 7 days, BC, CO.	Standard CBT. Weight and African Americans, smoking and weight concerns (super-gainers), minimizing weight gain (physical activity with limited resources, healthy food choices within soul food diet, recipes), deep breathing, RMC.

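### Assignment precedes consent, and consent and baseline measures are taken at an orientation that differs by arm, so the enrolled (ITT) set may be selected differently in the two arms

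*Protocol article*

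**What the plan says.** **Timing of assignment.** The Randomization section states: "Eligible participants receive a tentative random assignment and are scheduled for an orientation session, with only those who attend and provide written informed consent enrolled". The allocation is "randomly allocated using a 1:1 ratio in blocks of 50 to one of the two conditions", with the individual as the unit. The abstract (Methods/Design) says instead: "Enrolled participants are block randomized into one of two groups".

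**Planned yield.** The Randomization section says "We schedule up to 25 participants per group to ensure 8–12 tentatively assigned participants are enrolled/consented into the study". The section on orientation and intervention sessions gives a different group size: "We anticipate 8–16 participants per group".

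**What happens at orientation.** The same section says of participants: "They learn the background, purpose, format, and procedures of the study; provide informed consent; complete baseline measures". It then lists patch education and the CO and saliva samples, followed by general topics, and ends with an element for one arm only: "In the CS-CBT condition, we explain that the group is framed within a cultural context, designed to emphasize African American race/ethnicity and cultural issues". In the Orientation row of Table 1, the CS-CBT cell refers back to the CBT content and then adds "Race and smoking, views on research participation, distrust for biomedical research, concerns about nicotine replacement, goal setting, baseline assessment", followed by the samples and race-matched clinicians. The section on intervention conditions says that the control co-therapy team is not race-matched.

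**Use of the data.** Acculturation and ethnic identity are measured at baseline only (Table 2). They are the planned moderators, which the section on the present study calls exploratory. The ITT rule under Statistical analyses counts participants with missing data as smokers. It says nothing of people who were assigned but never enrolled.

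**The concern.** Randomization makes the arms comparable at the moment of assignment. Here the analysed set is formed later, at a session that is not the same in the two arms. If the session affects who consents, and if those who consent differ in their chance of quitting, the enrolled arms can differ before treatment starts. Counting missing as smoker does not repair this, because people who never enrolled are outside the count.

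The article itself supplies a plausible route. Its background reports that less acculturated smokers preferred culturally specific written materials and more acculturated smokers preferred standard ones. It also reports that standard CBT worked less well among smokers with traditional values. A trait linked to preference for an arm is thus also linked to outcome. The direction of any resulting bias cannot be predicted.

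The moderators raise a second issue. If acculturation and ethnic identity are reported after race and culture have been discussed in one arm only, the answers may already carry an effect of assignment, and the interaction tests would not rest on true baseline variables.

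**Working it through.** **1. Order of randomization and enrolment.** The abstract has enrolment, then randomization. The Randomization section has tentative assignment, then attendance and consent, then enrolment. Both cannot hold. The Randomization section is the more detailed text. Its numbers also fit assignment before enrolment: a block of 50 at 1:1 gives 50/2 = 25 per arm, the same as the maximum scheduled per group.

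**2. Planned loss between assignment and enrolment.** The article states counts and no percentage. Loss = 1 − enrolled/scheduled, at the maximum of 25 scheduled:

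| Enrolled per group | Share enrolled | Lost after assignment |
|---|---|---|
| 8 | 8/25 = 32% | 68% |
| 12 | 12/25 = 48% | 52% |
| 16 (the other group size given) | 16/25 = 64% | 36% |

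For the target of 247 enrolled, 247/0.48 ≈ 515 to 247/0.32 ≈ 772 people would be assigned, so about 268 to 525 would leave before ITT counting. With fewer than 25 scheduled the loss is smaller; for example, 20 scheduled and 8–12 enrolled is a loss of 40–60%.

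**3. How much of that loss can depend on arm.** The loss has two parts: not attending, and attending but not consenting. The welcome letters and reminder calls under Procedures are not described as arm-specific, and nothing says that the arm is disclosed before orientation. Only the second part is clearly open to arm-specific influence. The article gives no figure for it.

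**4. Illustration with no treatment effect.** All selection rates and prognoses here are assumptions. Half of those assigned have a good prognosis and half a poor one, and enrolled abstinence = Σ(prognosis × selection)/Σ(selection).

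*Arm-dependent selection acts on the whole loss* (control enrols 40% of both types; CS-CBT enrols 50% of good and 30% of poor):
- Prognosis 30%/14%: CS-CBT (0.30×0.5 + 0.14×0.3)/0.8 = 24.0%; control 22.0%; false difference 2.0 points.
- Prognosis 45%/5%: CS-CBT (0.45×0.5 + 0.05×0.3)/0.8 = 30.0%; control 25.0%; false difference 5.0 points.

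*Most loss is arm-blind non-attendance* (consent among attenders is 91% of both types in control; 100% of good and 82% of poor in CS-CBT):
- Prognosis 30%/14%: (0.30×1 + 0.14×0.82)/1.82 = 22.8% against 22.0%; 0.8 points.
- Prognosis 45%/5%: (0.45×1 + 0.05×0.82)/1.82 = 27.0% against 25.0%; 2.0 points.

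*Equal selection in both arms:* 0 points.

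The planned 12-month difference is 30% − 14% = 16 points.

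**5. Order of items within orientation.**

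| Source | Listed order |
|---|---|
| Text on orientation | study explanation, consent, baseline measures, patch education, samples, general topics, cultural framing (CS-CBT) |
| Table 1, CBT cell | study explanation, consent, topics, baseline assessment, samples |
| Table 1, CS-CBT cell | as CBT, then cultural topics, baseline assessment, samples, race-matched clinicians |

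Taken as sequences, the text and the CBT cell both put consent before the topics. The sources disagree on whether baseline measures come before or after the topics.

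**The case against.** The strongest reply is that the lists, read in order, place consent before the discussion of distrust of research and worries about nicotine replacement. A reader might infer that these topics drive consent; the documents do not support that. This part of the objection stands. What can still precede or accompany consent in CS-CBT alone is the presence of race-matched staff and, if it belongs to the study explanation, the cultural framing.

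A reader might also take the 52–68% as the size of the arm-dependent filter. It is not. It mixes non-attenders, who are not said to know their arm, with people who decline at orientation, and it uses the maximum number scheduled. That also stands.

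A third tempting reading is that the moderators are definitely measured after cultural content. Table 1's order suggests it and the orientation text suggests the opposite, so this is an ambiguity to resolve. The moderator analyses are exploratory, which limits the consequence.

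Finally, tentative assignment before orientation serves a practical need, since groups have to be scheduled and filled. That explains the early assignment. It does not explain why consent and baseline measures should share a session with arm-specific content and staff before the analysis set is fixed.

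**Conclusion.** The concern holds as a design weakness that the text itself sets out. Under the Randomization section, people are assigned first and enter the analysis only after attending and consenting at a session that differs by arm. The enrolled set may therefore be selected differently in the two arms, and the abstract contradicts this section on the order.

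Bias in the primary comparison is a risk and is not shown. It requires that selection at orientation differ by arm and be related to quitting. Under the assumed scenarios it ranges from 0 to 5 points against a planned 16. The documents do not say where in that range the trial lies, so the stronger statement, that randomization no longer protects the primary comparison, is not supported.

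That the ITT set means the enrolled is an inference from the Randomization section, since the analysis section does not define the set. For the moderators, the supportable conclusion is that they may be measured after arm-specific exposure and that the text and Table 1 must be reconciled.

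**What to change.** 1. Reconcile the abstract with the Randomization section on whether assignment or enrolment comes first, and reconcile the orientation text with Table 1 on the order of items.
2. Keep the tentative assignment for scheduling but do not disclose it.
3. Open orientation in both arms with one common script covering the study explanation, consent, all baseline questionnaires, CO and saliva. Where possible, have it led by existing staff who are not that arm's co-therapists. Only then confirm the allocation and begin arm-specific content.
4. Define ITT as everyone who consents before the arm is disclosed.
5. For cohorts already run, report the numbers assigned, attending and consenting by arm, and call the set modified ITT.

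**Cost.** The script of a 60-minute session needs an amendment, and some existing staff need rescheduling. Interventionists work in one condition only and race-matching is listed for the CS-CBT orientation, so concealment fails if the arm's own co-therapists open the session. Some participants will leave after learning their arm and will count as smokers.

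Counting everyone tentatively assigned as a smoker unless shown otherwise is not a good substitute. At 48% enrolment it would shrink 30% against 14% to 14.4% against 6.7%, and at 32% to 9.6% against 4.5%.
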